## Abstract

**Introduction:**

The first year after childbirth is a critical yet insufficiently monitored period for parental health. Postpartum mental and physical morbidity can affect both mothers and co-parents, but national longitudinal data remain scarce. The Stress Of Co-parents Related to A Traumatic Experience of birth across Switzerland (SOCRATES) cohort study aims to describe maternal and co-parental health and well-being trajectories during the first year after childbirth.

**Methods and analysis:**

SOCRATES is a prospective, population-based cohort study conducted in all linguistic regions of Switzerland. Eligible participants include women aged 14 and above who gave birth to a live or stillborn infant (≥22^+0^ weeks’ gestation and ≥500 g) and their cohabiting co-parents, provided they speak German, French, Italian or English. Recruitment was conducted in 81 of the 112 Swiss maternity units, birth centres and organisations of midwives over 6 weeks in spring 2025. Clinical data on pregnancy, childbirth and the early postpartum period are extracted from medical records. Postpartum hospitalisation data are obtained through linkage with national medico-administrative databases. Participants complete online questionnaires shortly after birth and at 2, 6 and 12 months post partum, including sociodemographic characteristics and patient-reported outcomes. The primary outcome is the prevalence of childbirth-related post-traumatic stress disorder at 2 months, assessed using the City Birth Trauma Scale. Secondary outcomes include depression, physical recovery, sexual health, quality of life, healthcare use, perceived care quality and overall well-being. A weighting procedure will be used to ensure representativeness and to account for attrition.

**Ethics and dissemination:**

Ethical approval was granted by all seven Swiss ethics committees (number 2024-02262). All participants provided informed consent. Findings will be disseminated through national and international conferences, peer-reviewed publications, policy briefs, social media and stakeholder engagement activities.

**Trial registration number:**

NCT06886841.

STRENGTHS AND LIMITATIONS OF THIS STUDYThis is the first national prospective cohort in Switzerland to assess the health and well-being of both mothers and co-parents during the first year post partum, with national representativeness supported by a multistep weighting procedure to account for non-participation and attrition.The study combines clinical data, multilingual patient-reported outcomes, linkage to national hospital administrative databases, and institutional-level survey data from maternity units, enabling multilevel analyses of physical, mental, sexual and social health, care practices and overall well-being.The study takes a comprehensive approach by examining both adverse health outcomes and positive indicators such as well-being, parental bonding, flourishing and life satisfaction.As with most observational longitudinal studies, reliance on self-reported measures may introduce recall or reporting bias, and loss to follow-up may limit data completeness.

## Introduction

 The first year after childbirth is a critical yet underaddressed period for parental health and family well-being.^1 2^ Postpartum care and research have traditionally focused on the first weeks after birth and on selected outcomes, particularly depression and short-term physical morbidity. This focus has left important gaps in knowledge about longer-term recovery, sexual and social health, care experiences and the needs of co-parents.^1 2^ Many women report unresolved complications beyond the early postpartum period, including fatigue, pain, sexual dysfunction and psychological distress.^2^,^4^ These sequelae can affect individual well-being, family life, partner relationship and caregiving capacity. Addressing these needs requires moving beyond a fragmented approach. Postpartum health can be conceptualised as a multidimensional process shaped by biological, psychological and social factors, as well as by care experiences and broader social and structural determinants, consistent with the biopsychosocial model,^5^ the WHO frameworks on social determinants of health and the WHO framework for quality of maternal and newborn care.^15^,^8^ This perspective supports the study of multiple interrelated domains over time, including mental health, physical recovery, sexual health, care experiences, social context and co-parent health.

Within this multidimensional approach, mental health constitutes a central component of postpartum health. It represents a major clinical and public health concern, with potential consequences for parents, infants and family functioning.^9 10^ Depression and anxiety affect a substantial proportion of mothers and co-parents,^9^,^11^ and some develop childbirth-related post-traumatic stress disorder (CB-PTSD), a subtype of PTSD with specific perinatal triggers.^12^,^14^ In Switzerland, a monocentric study with a small convenience sample reported that 20.7% of mothers and 7.2% of fathers met criteria for probable PTSD 1 month post partum.^15^ Although the study relied on a general PTSD screening tool and was affected by selection bias, it highlighted the potential magnitude of trauma symptoms and the clinical relevance of avoidance behaviours. Yet, long-term support remains limited, and trajectories of recovery are rarely monitored, despite their known consequences on quality of life.^3 16^ Avoidance and disengagement from care, recognised as key features of CB-PTSD, may also compromise help-seeking and widen existing gaps in support.

The quality and experience of care during childbirth and the postpartum period represent another key component of this framework, as they may shape health trajectories across multiple domains.^7 17^ According to the WHO, high-quality maternity care should be safe, effective, timely, equitable and people-centred and should integrate both provision and experience of care.^7 8^ Clinical practices during childbirth, such as labour induction, episiotomy, caesarean delivery or limited access to pain relief, have been associated with trauma, dissatisfaction and poor mental health outcomes.^18^ In Switzerland, postpartum follow-up includes an average of 7.9 home visits per mother, one of the highest rates in Europe.^19^ However, little is known about how the content and perceived quality of this care relate to health trajectories after childbirth. Despite growing attention to respectful maternity care, few population-based studies investigate how care provision and care experiences relate to long-term postpartum recovery, particularly in interaction with mental health, physical recovery and broader social determinants.^2 17^

### Study aims

This study aims to examine the evolution of the health and well-being of both mothers and co-parents during the first year after childbirth, using a population-based longitudinal design. Guided by the conceptual framework presented in figure 1, the study integrates mental, physical, sexual and social health outcomes with clinical data, care experiences and determinants measured at individual, health-system and structural levels.^15^,^8^ The primary objective is to (1) estimate the prevalence of CB-PTSD in both mothers and co-parents at 2 months post partum. The secondary objectives are to (2) assess depressive and anxiety symptoms from the perinatal period to 12 months postpartum and identify their early predictors; (3) evaluate maternal recovery, including early postpartum recovery, fatigue, pain and incontinence, as well as general health status in both parents; (4) describe sexual health at 6 and 12 months including sexual dysfunction and well-being; (5) assess trajectories of health-related quality of life and well-being in both parents; (6) examine how clinical practices at birth (eg, induction, mode of childbirth, perineal trauma) and structural characteristics (eg, staffing levels, care protocols, availability of support services), together with the perceived quality of intrapartum care (eg, communication, support, respect) influence health outcomes; (7) estimate the frequency and causes of maternal and neonatal hospitalisations, using linkage with national hospital discharge data and (8) analyse social and gender-related inequalities in postpartum health and well-being.

**Figure 1 F1:**
[figure not shown]
Study conceptual framework of postpartum health and well-being trajectories in the SOCRATES cohort. BW, birth weight; GA, gestational age; SOCRATES, Stress Of Co-parents Related to A Traumatic Experience of birth across Switzerland.

## Methods and analysis

This protocol was developed in accordance with the Standard Protocol Items Recommendations for Observational Studies (SPIROS) checklist.^20^ The study was registered on ClinicalTrials.gov under the study acronym ‘SOCRATES’ (Stress Of Co-parents Related to A Traumatic Experience of birth across Switzerland, NCT06886841). The registration was submitted on 12 March 2025 and last updated on 20 March 2025.

### Study design and population

The SOCRATES study is a nationwide, population-based, prospective cohort study conducted in Switzerland. The study is coordinated through a national collaboration between university-affiliated research teams and academic hospital partners in all linguistic regions, with the support of professional societies (ie, Swiss Federation of Midwives) and patient advocacy organisations (ie, Santé sexuelle Suisse and Periparto).

The study population comprises mothers and co-parents following childbirth. The term ‘mother’ is used solely to distinguish birthing individuals from their partners; any birthing person who meets the inclusion criteria, regardless of gender identity, is eligible. Mothers are eligible if they are aged 14 years or older and have given birth to one or more liveborn or stillborn infants at a gestational age of ≥22^+0^ weeks and with a birthweight ≥500 g. Co-parents are eligible if they are aged 14 years or older, their partner agrees to participate in the study and they are living together. As all study materials are provided in four languages (German, French, Italian and English), eligibility requires sufficient proficiency in one of these languages to ensure informed consent and valid questionnaire responses. Exclusion criteria are limited to refusal to participate or inability to provide informed consent.

### Sample size and power calculation

The required sample size was determined a priori based on the primary objective of estimating the prevalence of CB-PTSD in mothers at 2 months post partum. Assuming a prevalence of 5% in high-income countries^21^ and aiming for a 95% CI with a ±1% margin of error, we estimated that at least 1900 complete responses at 2 months would be needed. Anticipating a 60% follow-up rate, based on previous large-scale perinatal cohorts,^22 23^ we set a baseline recruitment target of approximately 3200 women. This sample size also allows for planned subgroup analyses on care practices.^24^

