### Statistical analysis and weighing procedure

Descriptive analyses will be conducted to summarise participants’ characteristics and outcomes. Associations between predictors and outcomes will be examined using multivariable regression models, accounting for potential confounders identified through literature review, clinical expertise and directed acyclic graphs. Sensitivity analyses will be performed to evaluate the robustness of the findings. Missing items will be imputed using standard procedures whenever relevant (eg, multivariate imputation by chained equations). All analyses will be carried out using statistical software such as R or Stata.

To ensure representativeness at the national level, we will apply a weighting procedure that includes the following steps. First, base design weights are computed to account for differences in participation across maternity care institutions. Second, raking is applied to align the weighted sample distribution with known population margins, using key sociodemographic variables (education, income, age, Swiss nationality and parity). Predictive models (eg, Random Forest, XGBoost, Support Vector Machines) are employed to impute missing values in these key variables before calibration. Third, non-response adjustment weights are estimated through logistic regression using region, parental origin, education, ethnicity, age, living conditions, institution type and number of pregnancies as predictors. Predicted response probabilities from this model are then used to construct inverse probability weights, such that respondents with a lower predicted probability of response receive larger weights. To prevent undue influence of extreme weights, trimming is applied at predefined thresholds. The final adjusted weights are then assigned to all observations for subsequent analyses.

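### The ±1% margin from 1900 responses assumes simple random sampling, with room for a design effect of about 1.04 at most, so the planned weighted prevalence is unlikely to achieve it

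*Protocol article*

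**What the plan says.** The section on sample size and power fixes the precision of the primary estimate. Its inputs are "Assuming a prevalence of 5% in high-income countries" and the criterion "aiming for a 95% CI with a ±1% margin of error, we estimated that at least 1900 complete responses", counted at 2 months. One further step follows, for loss to follow-up: "Anticipating a 60% follow-up rate, based on previous large-scale perinatal cohorts" leads to "we set a baseline recruitment target of approximately 3200 women". No allowance for unequal weights or for centre enters the figure.

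The section on statistical analysis and weighting describes how estimates will be formed. First, "base design weights are computed to account for differences in participation across maternity care institutions". Next comes raking to population margins on education, income, age, nationality and parity. Last come inverse-probability weights from a logistic response model, so that "respondents with a lower predicted probability of response receive larger weights". Extreme weights are trimmed, and the resulting final weights are carried into the later analyses. The section on recruitment reports 81 participating facilities out of 112.

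**The concern.** The sample size section describes the precision of an unweighted proportion from a simple random sample. The analysis section describes a weighted proportion from 81 centres. Weights that vary between women generally reduce the effective sample size, and correlation within centres can reduce it further. Neither loss is in the 1900.

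This matters because estimating the prevalence is the primary objective, and ±1 point around 5% is the only precision criterion the article gives for it. A reader who takes that margin at face value will expect a somewhat tighter interval than the planned estimator is likely to produce.

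**Working it through.** **Inputs from the article.** Prevalence p = 0.05; margin d = 0.01; 95% confidence; 1900 responses at 2 months; 60% follow-up; baseline target about 3200; 81 of 112 facilities.

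**Step 1: reproduce the stated figures.** n = z² p(1−p)/d².
- z = 1.96: 3.8416 × 0.0475 / 0.0001 = 1825.
- z = 2: 4 × 0.0475 / 0.0001 = 1900, the stated number.
- Baseline: 1900 / 0.60 = 3167, about 3200.

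The figures follow from the inputs with a design effect of 1.

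**Step 2: room left for a design effect.** The half-width is 1.96 × √(deff × p(1−p)/n). At n = 1900, √(0.0475/1900) = 0.005, so the half-width is 0.98 × √deff percentage points. It reaches 1 point at deff = (1/0.98)² = 1.04. With z = 2 there is no room at all, so 1.04 is the upper limit.

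**Step 3: what uses up that room.**
- Weighting alone: Kish's factor is 1 + CV². Setting it to 1.041 gives CV = √0.041 = 0.20.
- An illustration (assumed, not from the article): two equal halves of the population respond at 60% and 40%. Respondents are then 0.3 and 0.2 of the population, with weights 1/0.6 and 1/0.4. The weights sum to 0.5 + 0.5 = 1 and their squares to 0.3/0.36 + 0.2/0.16 = 2.083. Kish's factor is 0.5 × 2.083 / 1² = 1.042. One such difference exhausts the room.
- Centre alone: 1900/81 = 23.5 women per centre. Setting 1 + 22.5 × ICC = 1.041 gives an ICC of about 0.002.

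**Step 4: half-width at n = 1900 under assumed total design effects.** The article states neither a weight CV nor an ICC, so these are a range and not estimates.

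| Assumed deff | Half-width (points) | Effective n = 1900/deff |
|---|---|---|
| 1.0 | 0.98 × 1.000 = 0.98 | 1900 |
| 1.1 | 0.98 × 1.049 = 1.03 | 1727 |
| 1.25 | 0.98 × 1.118 = 1.10 | 1520 |
| 1.5 | 0.98 × 1.225 = 1.20 | 1267 |

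**The case against.** **Nothing is miscalculated.** This stands: 1900 follows exactly with z = 2. The mismatch is between the formula used and the estimator planned, not in the arithmetic.

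**The margin is a planning aim.** This also stands. A reader might infer that the weighted estimate cannot reach ±1 point. The article does not support that, because the achieved width depends on observed prevalence, responses and weights. At 4% prevalence and a design effect of 1.25, for example, 1.96 × √(1.25 × 0.04 × 0.96/1900) = 0.99 points. Under the article's own 5%, unlikely is the right word.

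**The size of the weighting loss is unknown.** A reader might infer that the estimate is heavily weighted because only about half of informed mothers consented. Low response does not by itself inflate variance: uniform 50% consent gives constant weights and a design effect of 1. Only variation in response does, and the article does not quantify it. Trimming limits the weights, and raking can recover precision where its variables predict the outcome. These points limit the size of the loss. They do not justify assuming none.

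**The clustering term may be small.** The usual ICC formula treats centres as a small random sample of clusters, whereas 72% of facilities took part. At an assumed ICC of 0.01 the increment is 22.5 × 0.01 = 0.22. If centres are viewed as sampled from 112, the factor 1 − 81/112 = 0.28 reduces it to about 0.06. The point does not depend on clustering.

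**A finite-population correction could offset the loss.** It would, if the target were the 6680 births in the recruitment window: 1825/(1 + 1824/6680) is about 1430. The weighting section aims at national representativeness, so that correction does not fit the stated target.

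**The reported interval may be computed correctly.** A reader might infer that the published interval will be too narrow. The article names no variance method, and an article may leave that choice to the full protocol or analysis plan. That silence is not the defect here.

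**Conclusion.** The point holds as a mismatch between the stated precision and the planned estimator. The 1900 responses give ±0.98 points only with a design effect of 1, and ±1 point survives a design effect of about 1.04 at most. With three layers of weighting, a weight CV above 0.20 is plausible, so the margin is unlikely to be achieved at 5% prevalence.

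The likely loss is modest. Relative to ±0.98, the assumed design effects of 1.1 to 1.5 add about 0.05 to 0.22 points (1.03 − 0.98 and 1.20 − 0.98). The absence of an allowance is certain from the text; its size is not. The finding concerns precision and shows no bias. It is also separate from the number of women actually recruited: all half-widths above keep the planned 1900.

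**What to change.** - In the sample size section, say that ±1 point assumes simple random sampling. Add the expected margin and effective sample size under an assumed design effect; a range is enough, for example ±1.03 to ±1.20 points and 1727 to 1267 effective responses for 1.1 to 1.5.
- Compute the primary confidence interval with a variance that reflects the final weights and centre, and record this wherever the estimator is specified.
- Report the achieved design effect with the primary result.

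The cost is a few sentences, standard survey-analysis code and a slightly less favourable stated margin. Recruitment is complete and no added enrolment is needed.

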### Recruitment and participation

Recruitment was conducted across 81 maternity units and birth centres, covering all linguistic regions and representing 72% of the 112 Swiss birth facilities. All centres recruited for a total of 6 weeks, with most conducting recruitment between 17 March and 27 April 2025. In some centres, recruitment periods were staggered due to local organisational constraints; however, all recruitment activities were completed by 11 June 2025. In each centre, a local investigator coordinated recruitment and data collection. All women giving birth during the recruitment period were systematically screened for eligibility. Eligible women received oral and written information after childbirth and were invited to provide electronic informed consent for (1) extraction of clinical data from medical records and completion of online questionnaires (with the option to consent to clinical data extraction only), (2) data linkage with hospital discharge records and (3) optional recontact after the first year for future research participation. Eligible co-parents were invited following the same procedures, except that consent for access to medical data and data linkage was not required.

Among 6680 women giving birth over the study period, 6609/6680 (98.9%) mothers were screened, and 5962/6609 (90.2%) were eligible (figure 2). The most common reason for ineligibility was language barriers (n=586/647; 90.6%). A total of 5488 mothers were informed about the study, 2835/5488 (51.7%) provided consent for extraction of clinical data, and 2785/5488 (50.7%) consented to complete the questionnaires. Of those, 2337/2785 (83.9%) started the baseline questionnaire, and 2122/2785 (76.2%) fully completed it. In parallel, 3863 co-parents were screened, 3792/3863 (98.2%) were eligible, 3206/3792 (84.5%) were informed, and 1321/3206 (41.2%) provided consent. Overall, 974/1321 co-parents (73.7%) started the baseline questionnaire, and 925/1321 (70.0%) fully completed it.

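### Weighting is claimed to give national representativeness, but the 8.9% of screened mothers excluded for language cannot be represented by any weight

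*Protocol article*

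**What the plan says.** **The claim.** The strengths and limitations box describes the cohort "with national representativeness supported by a multistep weighting procedure to account for non-participation and attrition". The section on statistical analysis and weighting puts it more strongly: "To ensure representativeness at the national level, we will apply a weighting procedure". The abstract also says that weighting will ensure representativeness. None of the three limits the claim to parents who speak a study language.

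**The eligibility rule.** Under Study design and population, "eligibility requires sufficient proficiency in one of these languages to ensure informed consent and valid questionnaire responses". The abstract names the same four languages.

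**The numbers.** Under Recruitment and participation, "6609/6680 (98.9%) mothers were screened" and "5962/6609 (90.2%) were eligible". The same paragraph adds: "The most common reason for ineligibility was language barriers (n=586/647; 90.6"%).

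**The weights.** There are three steps: base weights for differences in participation between institutions; raking to population margins, "using key sociodemographic variables (education, income, age, Swiss nationality and parity"); and inverse-probability weights from a logistic non-response model. The predictors of that model include region, parental origin and ethnicity. Neither list contains a language variable. The article does not say whether the margins describe all births or only births to women who met the language rule.

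**The limitations.** The box names self-report bias and loss to follow-up. It does not name the language exclusion.

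**The concern.** Weighting can correct for unequal chances of inclusion, but not for a zero chance. A mother without one of the four languages could not be enrolled, so no respondent carries information about her. All three steps redistribute weight among women who could take part. The strengths box itself describes the weights as dealing with non-participation and attrition, and ineligibility is neither.

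The claim therefore promises a property that the design does not have. At stake is the population to which the primary result applies. A reader who takes the wording at face value would apply the 2-month prevalence of childbirth-related PTSD to all births in Switzerland, whereas the design supports it for women able to answer in a study language. The confidence interval would not show the gap, because it covers sampling error only, and a larger sample would not reduce it.

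Co-parents appear to be touched as well. A co-parent is eligible only if the partner agrees to participate, so a co-parent whose partner was excluded for language seems to be lost even if the co-parent speaks a study language. The article gives no count for this.

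**Working it through.** **1. Reproduce the article's figures.**
- Ineligible mothers: 6609 − 5962 = 647, which agrees with the stated denominator.
- Eligible: 5962/6609 = 90.2%, as stated.
- Language among the ineligible: 586/647 = 90.6%, as stated.

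**2. Share of mothers excluded for language.**
- Of those screened: f = 586/6609 = 0.0887, or 8.9%.
- Of all 6680 women giving birth: 586/6680 = 8.8%.
- Both figures come from the participating facilities, 81 of 112. Nothing is reported on the language mix in the other 31.

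**3. What raking does with the excluded share.** Take one raking variable with categories c as a simplification. Let M be the population share of a category, e the part of that share made up of excluded women, and p_inc and p_exc the prevalences in included and excluded women of that category.
- True contribution of the category: (M − e) × p_inc + e × p_exc.
- Contribution after raking to a margin that covers all births: M × p_inc.
- Difference (raked minus true): e × (p_inc − p_exc).

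Summed over categories, the error vanishes if prevalence is equal in included and excluded women within every category. Otherwise it generally remains, unless differences of opposite sign happen to cancel. If the margins describe only language-eligible births, then e = 0 and no substitution takes place, but the estimate then refers to language-eligible women and is not national. The unrestricted claim is unsupported on either reading.

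**4. Size of plain under-coverage.** This step contains no raking term; it asks only how far the figure for included women could lie from the figure for all women. The input from the article is 5% prevalence, taken from the sample-size section and applied here to included women. The risk ratio RR in excluded women is an assumption; the documents give no figure for it.

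Overall prevalence = (1 − f) × 5% + f × 5% × RR

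| Assumed RR | Prevalence in excluded women | Overall | Shift (points) |
|---|---|---|---|
| 0.5 | 2.5% | 4.78% | −0.22 |
| 1.5 | 7.5% | 5.22% | +0.22 |
| 2 | 10% | 5.44% | +0.44 |
| 3 | 15% | 5.89% | +0.89 |

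**5. When the shift equals the planned margin.** The sample-size section aims for ±1 percentage point. Setting f × (p_exc − 5%) = 1 point gives p_exc = 5% + 1/0.0887 = 16.3%, a little over three times the prevalence in included women.

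**The case against.** The strongest reply is that nothing is hidden. The abstract, the eligibility section and the recruitment section all state the language rule, the recruitment section gives its numerator and denominator, and the rule has a sound reason. A reader can derive the 8.9%. On this view only one line in a short limitations box is missing. The disclosure is real, and it rules out any suggestion of concealment. It does not make an unrestricted claim valid: the eligibility text says who was enrolled, while the strengths box and the statistical section say whom the results represent, and the two differ.

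Other parts of the reply stand and limit the point:

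- **Raking.** A reader might infer that raking on nationality will make foreign women who speak a study language stand in for those who do not. The documents do not establish this. They do not identify the source of the margins, a detail that an article may leave to the full protocol, and they do not report the nationality, education or income of the 586 women. The effect is conditional on margins that cover all births. Nor is raking necessarily harmful here: if excluded women resemble included women of the same category more than they resemble the rest of the sample, raking moves the estimate towards the all-births value.
- **Direction.** A reader might infer that prevalence will be understated. No figure in the article supports either direction.
- **Size.** Every shift in the table is below 1 point, even at an assumed threefold risk.
- **Inequalities objective.** A reader might infer that objective 8 suffers most. That is plausible if language follows the social gradients it studies, but nothing in the article shows it, and many of its listed measures can be studied among eligible parents.
- **Coverage.** The 8.9% describes women screened in participating facilities, not all Swiss births.

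**Conclusion.** The point holds as a mismatch between the stated claim and the population that the design can reach. Mothers without a study language make up 8.9% of those screened in participating facilities, they had no chance of inclusion, and no base, raking or non-response weight can represent them. National representativeness is therefore not ensured, and the limitations do not say so.

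The numerical effect on the primary outcome is unknown in size and direction. The range of 4.78% to 5.89% rests on two assumptions: 5% prevalence in included women, and risk ratios of 0.5 to 3 in excluded women. Over that range the shift stays within the planned ±1 point. This is a matter of what the study may conclude and should be put right; it is not evidence that the prevalence estimate will be wrong.

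**What to change.** 1. Define the target population as parents able to answer in German, French, Italian or English, and limit the representativeness claim in the strengths box, the abstract and the statistical section to it. For co-parents, add that the partner must also be a participant.
2. State which population supplies the raking margins. Use margins that match the target population where they are available; otherwise state the assumption of equal outcomes within raking categories.
3. Give any all-births figure only as a secondary bounding range in both directions, for example risk ratios of 0.5 to 3 with a weight of 8.9%. Note that this weight assumes the same language mix in the 31 non-participating facilities.
4. Add the language exclusion, with 586/6609, to the limitations.

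Recruitment is complete, but the article still describes the weighting as something to be applied, so all four changes remain possible. The cost is a slightly narrower claim and one extra calculation.
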